#### Definition and modelling of abstinence rates

The quit rate is defined as the proportion of people achieving abstinence, with a denominator of all those who attended the service and set a quit date. Quitting is defined as prolonged abstinence, which is defined as allowing lapses during the first two weeks of the quit process measured according to the Russell standard[37]. Self-reporting is substantiated by biochemical validation using expired carbon monoxide (less than 10 parts per million)[38].

The modelling will follow the same approach as described above for calculation of usage rates, except that we will have a true denominator. We will therefore use multilevel logistic regression models rather than Poisson models.

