**Methods/design:**

This is a pilot cluster randomised controlled trial based in Birmingham, UK. Super output areas of Birmingham will be identified in which more than 10% of the population are of Pakistani and/or Bangladeshi origin. From these areas, 'natural geographical communities' will be identified. Sixteen aggregated agglomerations of super output areas will be identified, separating areas from each other using buffer regions in order to reduce potential contamination. These natural communities will be randomised to 'clinic + outreach' (intervention) or 'clinic only' (control) arms. The use of stop smoking services and the numbers of people quitting smoking (defined as prolonged self-reported abstinence at four weeks, three months and six months) will be assessed in each area. In addition, we will assess the impact of the intervention on adherence to smoking cessation treatments and patient satisfaction.

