#### Study questions

Primary study questions:

1. What are the rates at which the population of Pakistani and Bangladeshi male smokers will set a quit date with the stop smoking services in the intervention and control areas?

2. What proportions of those setting a quit date in the intervention and control areas achieve biochemically verified prolonged abstinence from smoking at a) 4 weeks, b) 3 months and c) 6 months after the agreed quit date?

3. What is the likely degree of contamination of the intervention and control areas and the design effects that need to be taken into consideration when conducting sample size calculations for a definitive cluster randomised controlled trial?

4. What are the key components of the intervention as it develops and how do these components relate to the outcome measured by the rates of setting quit dates and abstinence among those setting quit dates?

Secondary study questions:

5. What proportion of Pakistani and Bangladeshi male smokers that book an appointment with the stop smoking service attend the initial appointment and set a quit date in the intervention and control areas?

6. What smoking cessation treatments do Pakistani and Bangladeshi men use in the intervention areas, facilitated by outreach workers, and in the control areas, without such workers?

7. What are the experiences of the services of the relevant groups in each of the trial arms and how satisfied are they?

8. What proportions of those enrolled adhere to the interventions chosen?

9. What impact, if any, are these interventions likely to have on smokeless (oral) tobacco use in these smokers?

10. What are the costs, from a health service perspective, of delivering these interventions?

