#### 'Clinic + outreach' (intervention)

In areas allocated to the 'clinic + outreach' arm, the NHS stop smoking services will attract clients with additional support from four community based stop smoking advisors, also known as 'outreach workers'. These outreach workers come from the ethnic groups of interest (i.e. two of Bangladeshi origin and two of Pakistani origin) and live in the communities that they serve. Between them, they speak several relevant languages (i.e. Sylheti, Bengali, Punjabi, Mirpuri, Urdu and English).

A specialised training programme for the outreach workers will be organised prior to the start of the intervention, to combine training in smoking cessation with a special understanding of the norms and beliefs about tobacco in the Pakistani and Bangladeshi communities. This will consist of:

◦ Standard two-day SSA training delivered by HoB tPCT

◦ Three-day health promotion training course delivered by HoB tPCT on exploring ways to promote well-being and health, and techniques involved in the planning, preparation and delivery of approaches.

◦ Sessions given by primary care staff at the University of Birmingham on research skills, communication skills, the function of the NHS, the cultural context of the work, and discussion of the outreach role.

We envisage that the outreach workers will take the following approaches to improve the reach of and access to the smoking cessation services:

◦ Undertake community engagement work to help increase awareness of smoking cessation services

◦ Assist existing service providers with the delivery of stop smoking support and promotions

◦ Provide stop smoking support and medication for people in non-clinic venues, e.g. workplaces, public buildings.

Additionally, we envisage that the outreach workers will draw on their in-depth understanding of beliefs about and attitudes towards smoking, in order to:

◦ Raise awareness of the dangers associated with smoking and counsel smokers wishing to quit

◦ Identify suitable quit dates (which may be based on key religious events such as a Friday congregational prayer, journey on Umrah or Hajj (pilgrimage to Mecca), or to coincide with the month of Ramadan, for example)

◦ Highlight religious objections to smoking, where appropriate

◦ Make available existing and custom-made literature, telephone (Asian QuitLine) and other support materials.

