We hypothesise that the 'clinic + outreach' model will attract more patients to the service because it is seen as more culturally appropriate. In addition, the service should influence the proportion of people successfully attempting to stop smoking by encouraging patients to persist with treatment.

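### The arm comparison of abstinence is made only among men who set a quit date, which outreach is meant to increase, so it is open to selection bias in either direction

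*Protocol article*

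**What the plan says.** Study question 2 asks: "What proportions of those setting a quit date in the intervention and control areas achieve biochemically verified prolonged abstinence from smoking". The section on definition and modelling of abstinence rates sets the quit rate "with a denominator of all those who attended the service and set a quit date" and continues: "The modelling will follow the same approach as described above for calculation of usage rates, except that we will have a true denominator". The uptake model referred to there has arm, the log of the previous year's number setting a quit date, and a random effect for area. Abstinence is therefore compared by arm with the same structure, but in a logistic model.

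The intervention section states: "We hypothesise that the 'clinic + outreach' model will attract more patients to the service because it is seen as more culturally appropriate". It also attaches an effect to the proportion: "the service should influence the proportion of people successfully attempting to stop smoking by encouraging patients to persist with treatment". One listed activity is to "Provide stop smoking support and medication for people in non-clinic venues, e.g. workplaces, public buildings".

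The abstract says that "the numbers of people quitting smoking" will be assessed in each area. The outcome and analysis section gives no model for that count. Uptake, by contrast, is modelled with the log of the estimated number wishing to quit in each area as offset.

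**The concern.** Areas are randomised, but a man enters the abstinence denominator only after outreach has had its chance to act on him. The second quantitative primary outcome is thus conditioned on the first, which the intervention is intended to change. If men brought in by outreach have a different chance of quitting from men who would have come anyway, the two arms' setters are no longer comparable groups.

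The section on bias deals with contamination and information bias and does not mention selection into this denominator. At stake is how the abstinence result is read: a service that produces more verified quitters could show a lower quit rate than control, or one that helps no existing client could show a higher one.

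**Working it through.** The protocol states no quit rate, uptake effect or sample size, so there is no figure of its own to reproduce. All rates below are assumptions. The arithmetic pools areas, takes equal target populations in the two arms, and ignores clustering.

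**Notation.** Control has B setters with quit rate p0. With outreach, the same B men quit at b × p0, and (u − 1) × B added men quit at r × p0. Then:

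- rate among setters with outreach = p0 × [b + (u − 1) × r] / u
- ratio of service quitters over equal populations = b + (u − 1) × r

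**Simple case.** B = 100, p0 = 0.50, u = 1.5, b = 1, added men at 30% (r = 0.6).

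- Control: 50/100 = 50%.
- Outreach: (50 + 15)/150 = 65/150 = 43.3%.
- Odds ratio = (65/85)/(50/50) = 0.76.
- Quitters: 65/50 = 1.30.

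**Range with no effect on men who would set a date anyway** (b = 1, p0 0.20 to 0.50, u 1.25 to 2.0):

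| Added men's relative quit rate r | Odds ratio among setters | Ratio of quitters |
|---|---|---|
| 0.3 to 0.7 | 0.93 to 0.48 | 1.075 to 1.70 |
| 1.0 | 1.00 | 1.25 to 2.00 |
| 1.3 | 1.08 to 1.35 | 1.325 to 2.30 |

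The ends of the first row are p0 = 0.20, u = 1.25, r = 0.7 (rate 0.20 × 1.175/1.25 = 0.188, odds ratio 0.93) and p0 = 0.50, u = 2.0, r = 0.3 (rate 0.50 × 1.3/2 = 0.325, odds ratio 0.48). The last row shows the opposite distortion: an apparent benefit with none to existing clients.

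**With a real 10% relative benefit** (b = 1.1), the comparison still reverses when r < (u − 1.1)/(u − 1):

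- u = 1.25: 0.15/0.25 = 0.60
- u = 1.5: 0.40/0.50 = 0.80
- u = 2.0: 0.90/1.00 = 0.90

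For scale, Table 3 sums to 563 baseline users, or 281.5 per arm if split equally (the table does not give arm). With p0 = 0.40, u = 1.5, r = 0.5 and b = 1.1:

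- Control quitters: 281.5 × 0.40 = 112.6.
- Outreach quitters: 281.5 × 0.44 + 140.75 × 0.20 = 152.0, from 422.25 setters, a rate of 36.0%.
- Odds ratio = (0.36/0.64)/(0.40/0.60) = 0.84; quitter ratio = 152.0/112.6 = 1.35.

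**Prior-year adjustment.** The baseline covariate describes the year before outreach began. It can absorb stable differences between areas, but not a change of client mix that outreach produces during the intervention year.

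**The case against.** **Uptake is modelled too.** Setters per population times quitters per setter gives quitters per population. In the simple case, a reader who saw an uptake ratio of 1.5 beside 43% against 50% would not conclude that outreach yields fewer quitters. This stands for the point estimates. Two separate models do not, however, give an interval, intra-class correlation or design effect for the product, and design effects for the definitive trial are the subject of question 3.

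**Question 2 asks for exactly this proportion.** This stands. The proportion among setters is a valid description and a useful planning quantity for a pilot. The weakness is in modelling it by arm, with a causal expectation attached and no population-based companion.

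**The article is condensed.** A model for the abstract's count may exist elsewhere. That is possible, but the article does fix the abstinence model, and fixes it on the conditional denominator.

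**The added men need not be less likely to quit.** This stands. The background reports strong motivation and many attempts in these communities, and attributes failure to knowledge, beliefs and limited access. The hypothesis speaks of more patients, not different ones. That the mix changes is an inference from the outreach activities, such as support outside clinics.

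**Conclusion.** The point holds as an exposure to selection bias of unknown size and direction. It rests on the added men differing in their chance of quitting; if they do not, the odds ratio is undistorted. Under the assumed ranges above, the odds ratio among setters runs from 0.48 to 1.35 with no effect at all on men who would have set a date anyway.

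A reader might infer more, and the protocol does not support it:

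- That the comparison is biased, and towards harm. No quit rates are given, and the illustration is one assumed case among several.
- That quitters per population is the only contrast protected by the allocation. Uptake is area-based and equally protected.
- That the definitive trial will inherit a wrong effect size. Nothing says the odds ratio among setters will be used for that purpose.
- That the proportion among setters should be dropped. It answers question 2.

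**What to change.** Add, as the between-arm effect comparison for abstinence, the number of CO-verified abstainers per area at four weeks and at six months (the protocol amendments record that three-month follow-up was not possible). Use the Poisson random-effects model already described for uptake, with the log of the estimated number wishing to quit as offset. The offset is needed: the amendments say the allocation was switched so that outreach covered the larger target population, so raw counts are not comparable. The offset is an estimate, and counts the number wishing to quit rather than all residents, but it does not depend on uptake in the trial. A single quit-attempt share assumed for all areas cancels in the rate ratio.

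Adjust for the log of prior-year numbers setting a quit date, not prior-year quitters. The former is already a planned covariate and is non-zero in every area if the users in Table 3 are setters. Prior-year quitters are unsafe for two reasons: 11 of the 16 areas had only 2 to 11 users (66 in all), so some may have no quitters and an undefined log; and later follow-up was collected specifically for the trial, so no prior-year six-month value is shown to exist.

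Keep the proportion among setters as the answer to question 2, labelled as conditional on a post-allocation event and not to be read alone as an effect of outreach.

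The cost is one added model using the abstinence counts the planned analysis already needs. Its limits are an estimated denominator, sparse counts in the low-density areas, and no count of men who quit outside the service, so part of any gain could be displacement. Because the article says analysis was already under way, the addition should be dated and identified as such.

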#### Denominator for the proportion of smokers setting quit dates

Our overall aim is to develop and refine the intervention, to pilot it, and have the data needed to inform sample size calculations for a definitive trial evaluating these interventions. In order to perform sample size calculations for a future trial, we aim to assess the reach of the interventions in attracting smokers wanting to quit. For the purposes of this study, reach has been defined as the proportion of each relevant ethnic group setting a quit date using the stop smoking service, with the denominator for this being all those of relevant ethnic group attempting to quit during the same period. We are estimating this latter number as it cannot be directly measured. We have searched a variety of sources to give information on the proportion of each ethnic group that attempted to quit in the past year and these data are not available. No local survey can truly randomly survey Pakistani and Bangladeshi populations because there is no publicly available local sampling frame that records ethnicity. Consequently, we will use the Smoking Toolkit Study to provide relevant data on the proportion of people that attempted to quit in the past year for the general population and assume that this figure is approximately the same in Pakistani or Bangladeshi men[34].

Stop smoking services routinely record information about each of their patients, including their age, gender, ethnic group, type of service used, medication used and outcome. This will be used to give both a before and after measure of the use of the service by the relevant groups (i.e. males of Pakistani and Bangladeshi ethnic group). Thus, we will have, for each area, the rate of use of the service for 12 months prior to the intervention that will serve as a baseline variable in the analysis (see Table 3). The after measure will be the same data collected for the 12 months during which the outreach workers are active. These data will be supplied anonymously from BEN and HoBt PCTs and this does not rely on data collection developed for the study. As noted above, the before-after design will allow control for intrinsic variability between areas. As such there will be no attempt to assess baseline balance between the intervention and control areas.

**Table 3 T3:** Use of LSSS by randomisation area residents for the baseline period (1st November 2006 – 31^st ^October 2007)

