Area number	Number of Pharmacies	Numbers using any LSSS service 06/07	Number of smokers using LSSS within area they live	Number of smokers using LSSS in other areas of randomisation	Number of smokers* using LSSS users out of study zone	Number of smokers using unidentified LSSS
1	0	7	0	0	7	0

2	1	10	1	0	9	0

3	0	29	0	8	20	1

4	3	79	41	4	32	2

5	5	155	57	2	77	19

6	4	136	43	5	84	4

7	6	98	55	0	42	1

8	2	6	0	1	5	0

9	1	2	0	0	2	0

10	0	4	0	0	3	1

11	0	8	0	5	3	0

12	0	3	0	0	3	0

13	0	11	0	8	2	1

14	1	8	0	3	5	0

15	0	2	0	0	2	0

16	0	5	0	0	5	0

*Bangladeshi or Pakistani Males aged 18 years or over

Although we will estimate the proportion of people setting a quit date, we cannot truly know the denominator, as in many cases people set multiple quit dates, hence we will consider this a rate and the 'denominator' an offset in the analysis.

Quantitative analysis will use a multilevel approach. In this model the outcome variable will be the number of individuals setting a quit date in each of the 16 randomised areas. The quasi-denominator is the estimated number wishing to quit in each area, and the log of this number will be used as an offset in a Poisson regression model. Independent variables in the model will be the group (control or intervention) and the log of the numbers setting a quit date in the previous 12 months before the trial. The randomised areas will be included in the model as a random effect, thereby allowing for the clustering inherent in the design[35]. This will be used in estimating the intra-class correlation coefficient, which in turn will determine the design effect. This is the multiplier which has to be applied to standard sample size formulae to allow for the effect of randomising at the cluster level instead of the individual level[36]. The stratification used in producing the randomisation will not be utilised in the analysis.

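### The abstinence model uses no individual covariate although age and ethnic group are recorded, so chance case-mix differences between a few large areas can distort this one allocation's arm comparison and cost precision

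*Protocol article*

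**What the plan says.** The section Definition and modelling of abstinence rates takes as denominator all men who attended and set a quit date. It then states "The modelling will follow the same approach as described above for calculation of usage rates", with one change because the denominator is now a true one: "We will therefore use multilevel logistic regression models rather than Poisson models".

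The approach referred to is set out under Denominator for the proportion of smokers setting quit dates: "Independent variables in the model will be the group (control or intervention) and the log of the numbers setting a quit date" in the 12 months before the trial. It continues "The randomised areas will be included in the model as a random effect, thereby allowing for the clustering inherent in the design", and adds "The stratification used in producing the randomisation will not be utilised in the analysis". Neither section names an individual-level term.

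The same section says that the services "routinely record information about each of their patients, including their age, gender, ethnic group". For differences between areas it relies on the prior year, saying that "the before-after design will allow control for intrinsic variability between areas", and on that ground it plans no assessment of baseline balance. Table 2 describes abstinence beyond four weeks as data gathered for the trial, so no prior-year value of it is described.

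**The concern.** The outcome belongs to individual men, but the covariates come from a model for area counts. A prior-year count of quit dates says how busy an area was. It does not say how old the trial-year men were, or how many were Pakistani and how many Bangladeshi. Both characteristics are fixed for each man before treatment, and the dataset's eligibility rules cannot be applied without knowing age and ethnic group.

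This would matter little with many areas of similar size. Here a handful of areas carries most of the men, so the arms may differ in age or ethnic mix by chance. If quit rates also differ by age or ethnic group, part of the observed arm difference in abstinence would reflect who the men were rather than what outreach did, in either direction.

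**Working it through.** The protocol states no sample size, power, quit rate or intra-class correlation, so there is no planned figure to reproduce.

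**1. Concentration (Table 3, numbers using any service in the baseline year).** All 16 rows add up; the total is 563.
- Areas 4 to 7: 79 + 155 + 136 + 98 = 468, and 468/563 = 83.1%.
- Sum of squared area sizes: 6,241 + 24,025 + 18,496 + 9,604 = 58,366 for areas 4 to 7, plus 1,333 for the other twelve, giving 59,699.
- Effective number of areas: 563²/59,699 = 316,969/59,699 = 5.3 of 16.

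**2. Possible chance imbalance in case mix.** Let *s* be the between-area SD of the share of some subgroup (one ethnic group, or older men). The documents do not give *s*. For a user-weighted comparison,

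SD(arm difference in share) = *s* × √[Σ_A(n_i/N_A)² + Σ_B(n_i/N_B)²].

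With an even split (N_A = N_B = 281.5), the root is √(59,699/281.5²) = √(59,699/79,242) = 0.868. The last two columns come from 20,000 simulated allocations: 2:2 within four size-ranked blocks (a stand-in for the real strata), with area shares normal about 50% and truncated to 0–100%.

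| Assumed *s* | Formula | Simulated SD | Chance of exceeding 10 points |
|---|---|---|---|
| 10 points | 8.7 | 8.6 | 0.25 |
| 20 points | 17.4 | 17.0 | 0.56 |
| 30 points | 26.0 | 23.5 | 0.68 |

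**3. Resulting shift in the arm difference.** Shift = (arm difference in subgroup share) × (subgroup difference in quit rate). The quit-rate gap is also assumed, at 5 to 15 points.
- 10-point imbalance: 0.5 to 1.5 points.
- 20-point imbalance: 1 to 3 points. With a 10-point gap and a better-subgroup quit rate of 40%, the arms sit at 36% and 34%, an odds ratio of (0.36/0.64)/(0.34/0.66) = 1.09.
- 40-point imbalance: 2 to 6 points.

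For scale, the standard error of an arm difference at a 40% quit rate, ignoring clustering, is √(2 × 0.4 × 0.6/281.5) = 4.1 points.

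**4. What adjustment buys.** Simulation of 1,500 runs with Table 3 sizes, 2 v 2 allocation in four assumed strata, no true arm effect, a subgroup share uniform on 10–90% in each area, and a subgroup log-odds gap of 0.6. The fits were ordinary logistic regressions without the random effect, so they show the spread of the estimate and not the behaviour of the multilevel standard error.

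| Adjustment | SD of arm log-odds ratio |
|---|---|
| None | 0.213 |
| Log baseline count | 0.215 |
| Area's baseline quit rate | 0.218 |
| Individual subgroup | 0.183 |

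The mean was about 0 in every row. Individual adjustment cut the SD by 1 − 0.183/0.213 = 14%, or 1 − (0.183/0.213)² = 26% of the variance. The area-level terms removed nothing. Redrawing the area shares between the two years gave much the same (0.212, 0.214, 0.226, 0.180). Areas differed here only through case mix, so the relative gain is at the favourable end.

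**The case against.** The strongest reply is that arm, a baseline term and a random area effect make a legitimate primary model for a pilot cluster trial, and that further covariates may be listed in an analysis plan that is not shown. The first half stands. The second stands only in part: the article does not leave the covariates open. It lists them for the usage model and carries that approach into the abstinence model.

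A reader might infer that case-mix differences pass unchecked into the arm effect as bias. The documents do not support that. Allocation is random within strata, so such imbalance averages to zero over allocations, as the simulated means show, and the random effect places between-area variation, case mix included, in the standard error. What remains is that one allocation can still be unbalanced by an unknown amount, and that a between-area variance resting on about five effective areas is itself poorly estimated. The switch of arms reported under Protocol amendments is a separate matter. It was prompted by population size, and nothing in the article shows age or ethnic mix by area, so it is not relied on here.

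The magnitudes are fairly criticised: the spread of case mix, the quit-rate gap and the strata used in the calculations are all assumed. User weighting also gives the large areas more dominance than a random-effects fit would if between-area variance is appreciable.

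A reader might also infer that omitting the covariates wrongly inflates the between-area variance, and so the design effect asked for in study question 3. It does not. Case mix is part of real clustering, and the unadjusted variance is the right input for a definitive trial analysed without adjustment.

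Finally, men enter the denominator after allocation, by setting a quit date, and outreach may change who does so. Adjustment deals with that only in part.

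**Conclusion.** The point holds as a worthwhile improvement to a stated specification; the planned model is not invalid. It has no individual covariate, the inherited count describes neither case mix nor prior abstinence, and four areas supply 83% of baseline users. Chance differences in age or ethnic mix can therefore distort this allocation's comparison and cost precision.

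The size cannot be derived from the documents. Under the assumptions shown, plausible shifts are about 1 to 3 points for a 20-point imbalance, which is below the 4.1-point unclustered standard error, and the saving in SD is around 14%. Both rest on assumed subgroup shares and quit-rate gaps and on baseline-year user numbers standing in for the trial year. A claim of systematic bias would go beyond what the article supports.

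**What to change.** In Definition and modelling of abstinence rates, state that the multilevel logistic model is fitted on individual records, with arm, the baseline term, age and ethnic group (Pakistani or Bangladeshi) as fixed effects and area as the random effect. Report the model without age and ethnic group beside it.

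- Do not adjust for medication or type of service, which follow allocation.
- Label the adjusted analysis by when it was specified, since Current study status says that analysis of the primary outcomes was already under way.
- Note that adjustment only partly addresses any change in who sets a quit date after allocation.
- Report the between-area variance from both models. Use the unadjusted one to plan a definitive trial analysed without adjustment, and the adjusted one for a trial analysed with it.

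The cost is a few sentences of analysis wording. The services already record both variables, and two extra individual-level terms are a negligible burden with several hundred men.
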